### Recruitment

The study team will promote the study through flyers, word of mouth, and advertising in newsletters, webpages, and on various social media platforms via existing networks. Sites may contact the research team if they are interested in participating. The research team will also send invitation emails to residential aged care providers. Information sessions will be provided to potential participating sites which will be conducted either on site or online. If a residential aged care provider expresses interest in participating as a site, they will first be required to complete a demographic survey to determine their eligibility and site characteristics prior to randomisation. We acknowledge that this recruitment approach may result in a sample biased towards providers who are motivated to improve catheter care practices and are willing to allow researchers to monitor staff and organisational performance.

### Randomisation

An independent statistician at a separate institution will perform block randomisation, stratified according to three site sizes (small, medium, and large). Blocks will be randomly sized either two or four. The randomisation sequence will be generated in R. The National Ageing Research Institute (NARI) team will remain blinded to the allocation sequence and provide the statistician with numerical site study IDs and corresponding size values. The NARI research team will inform each aged care provider whether they have been allocated to the intervention group or control group following randomisation. As this study concerns the implementation of training resources vs usual care, it is not possible to blind the entire research team or sites to their group allocation. Only the Project Manager and three Research Assistants will have access to information about all sites’ group allocation. The rest of the research team, including the Chief Investigator and the statistician, will remain blinded to the identities of sites for the duration of the trial and subsequent statistical analysis of trial data.

### Intervention

Participants (managers/senior leaders, nurses, and PCWs) at intervention sites will access all elements of the *Bundle*. The *Bundle* will be implemented in two consecutive phases, (1) education phase and (2) application to practice phase.

### Phase 1: education

Phase 1 is designed to take account of managers’/senior leaders’, nurses’ and PCWs’ different roles and responsibilities. Education comprises an online catheter care course for nurses, an in-person catheterisation skills workshop for nurses delivered by CHA, an online catheter care course for PCWs, and a catheter care toolkit for managers and senior leaders.

#### The online catheter care course for nurses

The online catheter care course for nurses is self-paced and takes 5–8 h to complete. It comprises 5 modules addressing the following competencies: (1) emotionally supporting a person living with an IDC, (2) applying clinical decision making prior to urinary catheterisation, (3) understanding and applying principles of insertion and/or removal of a urethral or changing a suprapubic catheter, (4) knowing and implementing evidence-based nursing interventions to promote physical wellbeing, (5) minimising and troubleshooting common issues related to urinary catheterisation. The learning material was validated by advanced practice nurses.

#### The catheterisation skills workshop for nurses

The catheterisation skills workshop has been designed for nurses by CHA and will be delivered by facilitators who are advanced practice nurses who have advanced clinical skills or knowledge in continence or urology nursing. The workshop includes practice of indwelling catheterisation insertion on both male and female manikins as well as changing a suprapubic catheter. Workshop facilitators use a comprehensive checklist to assess learners and provide feedback on areas for development to each learner, based on their performance. The workshops will be conducted either on-site or at a nearby alternative venue if required. The number of nurses able to attend each workshop is limited to four due to the intensity of the program.

#### The online catheter care course for PCWs

Participating PCWs at the intervention sites will complete their own online course that consists of three learning modules that have been designed to take account of their roles and responsibilities in residential aged care homes. The learning material was validated by PCWs. We estimate it will take up to 1 h to complete each module. The content is interactive and includes a combination of text, short videos, quizzes, and scenario-based reflective exercises.

#### The catheter care toolkit for managers and senior leaders

The toolkit is a knowledge translation resource that is designed to support residential aged care managers and senior leaders to coordinate, supervise, and manage catheter care in the workplace. It includes the following resources to assist them to implement, evaluate and sustain the intervention:Information about the clinical risks associated with IDCsThe components of the *Bundle*The knowledge and skills nurses and PCWs require to deliver person-centred catheter careA Catheter Care Audit Tool to assist self-assessment of their organisational capacity to deliver person-centred urinary catheter care.

Given the lack of evidence and guidance about IDC care in the residential aged care setting, we anticipate site management will require the information to influence the quality of catheter care.

### Phase 2: application to practice

Phase 2 runs for 3 months after participating staff from each site have completed the course and workshop. Three advanced practice nurses with expertise in catheter care will provide coaching support over 3 months. The level and frequency of support will be planned with each participant and will be influenced by their role, responsibilities, scope of practice, how many residents with IDCs they are caring for and their overall baseline experience managing IDCs. Coaching will be available on an individual basis and offered online and by phone, depending on the nurses’ and managers’/senior leaders’ individual preferences. The frequency will also be flexible and responsive to their preference.

### Comparator

Sites assigned to the control arm will continue with usual care during the trial period. After data collection is complete at their site, they will be given access to all the resources of the *Bundle* except the Catheterisation Skills Workshops for nurses about catheter insertion. If they wish to complete the workshop after the research has been concluded, they will be referred to CHA to discuss their individual needs.

### Adherence

Adherence to the intervention will be monitored by (i) online learning management system’s reporting and analytics features; (ii) workshop attendance records; and (iii) completion of data collection at each time point. Intervention fidelity will be assessed through qualitative semi-structured interviews with participants, workshop facilitators, and experts delivering the online/phone support.

### Outcome measures

#### Primary outcome

The primary outcome is the feasibility of implementing the intervention (*IDC-IMPROVE Catheter Care Bundle*) into Australian residential aged care homes. The following feasibility outcomes will be assessed as a composite primary outcome: (i) the acceptability of the *Bundle*, (ii) the fidelity of the implementation, (iii) the compatibility of the *Bundle* with standard aged care home IDC care.

Measures related to the feasibility and acceptability of both the trial and the *Bundle* are outlined in Table 1. Data collection timepoints are provided in Table 2. The feasibility of conducting a definitive cRCT is assessed against a priori progression criteria outlined in Table 3. If thresholds are not met, other qualitative data may be used to inform modifications of the *Bundle* and the trial design.

**Table 1 Tab1:** Description of instruments, timepoints, and target groups for data collection

Timepoint	Intervention	Control	Instrument	Description
Site and participant demographic information				
t_0_	X	X	Aged care home demographic survey	Basic information on size, ownership and staff numbers
t_0_	X	X	Nurse/PCW Demographic Survey	Basic information on qualifications, years in nursing, years in aged care etc.
Clinical data collection tools				
t_0_, t_1_, t_2_	X	X	IDC-IMPROVE Nurses’ Catheter Care Knowledge and Confidence Scale (KCS-Nurse)	The KCS-Nurse is a newly developed scale that contains 51 items to measure nurses’ self-reported knowledge and confidence to deliver person-centred IDC care
t_0_, t_1_, t_2_	X	X	IDC-IMPROVE PCW Catheter Care Knowledge and Confidence Scale (KCS-PCW)	A newly developed scale that contains 34 items to measure PCWs’ self-reported knowledge and confidence to deliver person-centred IDC care
t_1_	X	X	Nurse Professional Competence (NPC) Scale Short Form	The NCP Scale-SF is a reliable and valid tool with 35-items that measures nurses’ self-reported competence in 6 key domains. Will be completed by nurses via survey. Findings to be correlated with the KSC-Nurse to establish the convergent validity of the KCS-Nurse
t_0_, t_1_	X	X	IDC-IMPROVE Clinical Data Extraction Form	Clinical information about age range, gender, IDC type, reason for IDC, duration of IDC, number of IDC changes, disciplinary background of staff who perform the change, number and type of IDC-related complications, and number of admissions to hospital and emergency departments for IDC-related complications for residents with an IDC for the prior 3 months, to be completed by managers/senior leaders or RNs
Feasibility and sustainability data collection tools				
t_0_, t_2_	X	X	IDC-IMPROVE Catheter Care Audit Tool	A pre and post intervention audit of each aged care home, IDC-related organisational policies and practices, to be completed by managers/senior leaders and administered with the aged care home demographic survey
t_0_, t_1_, t_2_	X		Participant Completion and Withdrawal Record	Number of nurses and PCWs who enrol, complete or withdraw from the education or application to practice phase
t_1_	X		Online Catheter Care Course for Nurses Feedback Survey	Rating scale to capture nurses’ satisfaction with the content and questions on their experience of the course
t_1_	X		Catheterisation Skills Workshop Feedback Survey	An online survey nurses will be asked to complete at the end of the catheterisation skills workshop
t_2_	X		Semi-structured qualitative interviews	Interviews will be conducted with nurses, PCWs and managers exploring participants’ perspectives and experiences with the *Bundle*, barriers and enablers to implementing the trial, contextual factors affecting IDC care and implementation of the *Bundle*

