### Feasibility cRCT

This is a multi-centre, facility-level cluster randomised control feasibility trial with an embedded process evaluation conducted in residential aged care homes in Australia. After baseline data are collected for all outcome measures, 12 aged care homes will be randomised to receive the intervention and 12 will continue to provide usual practice (control). Each cluster comprises one site (residential aged care home). The control sites are included to assess acceptability of randomisation and fidelity to data collection and to provide a comparator for pilot data. Control sites will receive some elements of the *Bundle* after the trial closes and data collection is completed at their site. Figure 1 provides an overview of the trial.

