#### IDC-IMPROVE Nurses’ Catheter Care Knowledge and Confidence Scale (KCS-Nurse)

All participating nurses will complete the KCS-Nurse scale at t_0_, t_1_, and t_2_. This scale was developed for this study to assess aged care nurses’ knowledge of, and confidence related to urinary catheters and catheter care. It comprises two sections: confidence and knowledge. The confidence section is theoretically informed by five key competency domains: (1) ability to psychologically support a person living with a long-term urinary catheter; (2) ability to apply clinical decision-making prior to urinary catheterisation; (3) understanding and application of principles for inserting and/or removing a urethral or suprapubic catheter; (4) knowledge and application of evidence-based nursing interventions to promote physical well-being; and (5) ability to minimize and troubleshoot common issues related to long-term urinary catheterisation. This section includes 21 statements regarding nursing actions specific to catheter care and uses a 5-point Likert scale (ranging from 0 for “no confidence” to 5 for “high confidence”) to capture responses; the highest possible score for these 21 statements is 105. The knowledge section includes 30 items with a dichotomous measurement scale, where a correct answer scores 1 and an incorrect or uncertain answer scores 0, resulting in a highest possible score of 30. A survey of 11 experts conducted by the research team has already demonstrated strong content validity (S-CVI/Ave = 0.97). Internal validity, construct validity, and convergent validity of the scale will be estimated in this study.

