### Data analysis

Feasibility outcomes will be analyzed using quantitative and qualitative approaches. The R software program will be used for all quantitative data manipulation and analysis. Descriptive analysis will be conducted for all demographic and scaled outcomes, reporting at baseline (t_0_), post-intervention (t_1_), and follow-up (t_2_) timepoints. The KCS-Nurse scores will be assessed for normality using descriptive statistics and histograms. All subscale scores will be analysed using the median with the 25th and 75th percentiles (IQR), and normally distributed scores will be additionally analysed with means and 95% confidence intervals (CI). Discrete and categorical data will be analysed using frequencies with relative frequencies. Descriptive analyses will be assessed according to progression criteria and reported against the prescribed thresholds in Table 3.

Survey feedback will be summarised. Qualitative interview data will be recorded, transcribed verbatim, checked for accuracy, and analysed using thematic analysis [21]. Two members of the research team will analyse the data independently and conduct a thematic analysis. Qualitative findings will be used alongside the analysis of progression criteria and feedback from surveys to conduct a process evaluation. This will explore how the intervention was experienced by participants and any changes that they think would improve the trial and intervention and their implementation. A “Framework” analytical approach [22] informed by the 14-domain version of the Theoretical Domains Framework [23] and based on the research objectives will be used to describe the feasibility of the *Bundle*.

The internal consistency, construct validity and convergent validity of the KSC-Nurse will be analysed. Internal consistency will be estimated using Cronbach’s alpha. Construct validity will be estimated using confirmatory factor analysis (CFA), based on the 5 key competency domains of the scale. The model fit will be assessed using the Comparative Fit Index (CFI). Convergent validity will be estimated by calculating the Pearson correlation coefficient between the KSC-Nurse and the Nurse Professional Competence Scale-Short Form (NPC Scale-SF) [24], accounting for clustering. The intra-cluster coefficient (ICC) will be calculated based on KSC-Nurse scores to explore clustering effects and inform implementation of the instrument in other studies.

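### The convergent-validity comparator (NPC Scale-SF) is scheduled only after training, so a KCS-Nurse correlation across arms that ignores arm may partly reflect the Bundle's effect

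*Protocol article*

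**What the plan says.** In Table 1 (Outcome measures), the row for the "Nurse Professional Competence (NPC) Scale Short Form" carries the single timepoint t1, marked for intervention and control. Its purpose is given there: "Findings to be correlated with the KSC-Nurse to establish the convergent validity of the KCS-Nurse". The KCS-Nurse is taken three times: "All participating nurses will complete the KCS-Nurse scale at t_0_, t_1_, and t_2".

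The Data analysis section defines the timepoints as "reporting at baseline (t_0_), post-intervention (t_1_), and follow-up (t_2_) timepoints". It gives the method as follows: "Convergent validity will be estimated by calculating the Pearson correlation coefficient between the KSC-Nurse and the Nurse Professional Competence Scale-Short Form", with clustering taken into account. It names neither the arm nor the KCS-Nurse timepoint to be used.

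On exposure, the section on the nurses' online course says "It comprises 5 modules addressing the following competencies: (1) emotionally supporting a person living with an IDC" and lists four more. The Comparator section says "Sites assigned to the control arm will continue with usual care during the trial period". Validating the KCS-Nurse, including its convergent validity, is the fourth of the five objectives in Methods.

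**The concern.** A convergent-validity coefficient should describe the scale: do nurses who score high on the KCS-Nurse also score high on an established competence measure? Here the only same-time pair of scores comes after randomisation and after training. One arm has been taught material that matches the scale's own confidence domains, and the other has not.

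If training raises KCS-Nurse scores but hardly moves general competence, combining the arms adds KCS variance that is unrelated to the NPC, and the correlation falls. If training raises both self-ratings, the shared shift between arms can push the correlation up. In either case the coefficient depends partly on how well the Bundle worked. At stake is the interpretation of one objective 4 result for a scale that the authors hope to see used in other studies. The timing also cannot be repaired in the analysis: a t0 NPC score that was never collected cannot be recovered.

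**Working it through.** **The plan's own figure.** The protocol states no expected value or precision for this correlation. Its one sample size figure, 62 nurses, is for the completion rate. It reproduces as 1.96² × 0.80 × 0.20 / 0.10² = 61.46, rounded up to 62. It does not bear on this point, except that 62 and the target of 96 serve below as sample sizes.

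**Inputs from the protocol.**
- NPC Scale-SF at t1 only, both arms (Table 1).
- t1 is post-intervention (Data analysis). Table 1 also places the course and workshop feedback surveys at t1, which confirms that training comes first.
- 12 intervention and 12 control homes (Feasibility cRCT), with at least four nurses sought per home and 96 in total (Nurses).
- The five course modules and the five KCS-Nurse confidence domains cover the same topics in the same order.

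**Assumptions (not in the protocol).** Equal arms; unit SD within arm on both scales; a common within-arm correlation r; training shifts the KCS-Nurse mean by d SD and the NPC mean by g SD. Ranges: d from 0.5 to 1.5, g from 0 to 1, r from 0.3 to 0.7.

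**Formula.** With equal arms, the arm difference adds d²/4 and g²/4 to the two variances and dg/4 to the covariance:

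pooled r = (r + dg/4) / √[(1 + d²/4)(1 + g²/4)]

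**Examples at r = 0.50.**
- d = 1, g = 0: 0.50 / √1.25 = 0.447
- d = 1.5, g = 0: 0.50 / √1.5625 = 0.400
- d = 1, g = 0.25: 0.5625 / √(1.25 × 1.0156) = 0.499
- d = 1.5, g = 1: 0.875 / √(1.5625 × 1.25) = 0.626

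**Grid at r = 0.50.**

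| KCS shift d | g = 0 | g = 0.25 | g = 0.5 | g = 1 |
|---|---|---|---|---|
| 0.5 | 0.485 | 0.511 | 0.529 | 0.542 |
| 1.0 | 0.447 | 0.499 | 0.542 | 0.600 |
| 1.5 | 0.400 | 0.471 | 0.534 | 0.626 |

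Over the same shifts, r = 0.3 gives 0.240 to 0.483 and r = 0.7 gives 0.560 to 0.769.

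**Does accounting for clustering deal with it?** A simulation of 24 homes with four nurses each (true r = 0.50, assumed ICC 0.1, 1,500 replicates) gave these mean correlations:

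| d, g | Ignoring arm | Adjusted for arm | Within home |
|---|---|---|---|
| 1, 0 | 0.444 | 0.497 | 0.494 |
| 1, 0.25 | 0.498 | 0.498 | 0.499 |
| 1, 0.5 | 0.540 | 0.497 | 0.495 |
| 1.5, 0 | 0.393 | 0.493 | 0.493 |

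Arm is constant within a home, so a within-home correlation removes the mean shift, as does adjustment for arm. A method that changes only the standard error leaves the shift in place.

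**Against sampling error.** For r = 0.50 the 95% interval by Fisher's z, ignoring clustering, is 0.333 to 0.637 at n = 96 and 0.286 to 0.667 at n = 62. Every entry in the r = 0.50 grid lies inside both intervals.

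**The case against.** The strongest reply is that the protocol never says the arms will be pooled without adjustment. That stands: pooling is an inference from silence. Accounting for clustering could mean a within-home correlation, which removes the shift. The authors also keep nurses who miss the workshop separate from those who attend, so they are alert to differences in exposure. The exact model could reasonably be left to an analysis plan that is not shown. The timing of the form is different: Table 1 fixes it.

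A second reply is that the bias is unproven and small beside the sampling error. This also stands in part. The shifts are assumptions, and a 1 SD shift on the KCS-Nurse with 0.25 SD on the NPC gives 0.499 against 0.50. But bias inside a confidence interval is still bias, and recruiting more nurses would not remove it.

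A third is that the schedule is only partly visible. Table 2 is not shown, and the Feasibility cRCT section says baseline data are collected on every outcome measure before randomisation, which could be taken to include the NPC Scale-SF. Table 1 nevertheless lists t1 alone for this form, so this lowers certainty slightly without answering the point.

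A reader might also infer that Cronbach's alpha, the factor analysis and the ICC suffer from the same fault. The protocol does not support that: it names no timepoint for those analyses, so baseline data may already be intended. Ceiling effects or a changed spread of scores among trained nurses are possible, but nothing in the document shows them.

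**Conclusion.** The point holds as a conditional one. The only same-time pair of KCS-Nurse and NPC scores is post-training, half the homes have by then been allocated training on the scale's content, and the protocol does not commit to handling arm. A correlation across arms that ignores arm may therefore be biased by the intervention. For a within-arm correlation of 0.50, the pooled value runs from about 0.40 to 0.63 over the assumed shifts. It can be too low, too high or about right.

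It would be tempting to say that the coefficient is certainly distorted. The documents do not support that, because they give no training effect on either scale and do not rule out a within-home analysis. Nor is the progression decision at risk: the only psychometric criterion in Table 3 is internal consistency of the KCS-Nurse. This is an inexpensive improvement to one objective 4 result and does not threaten the trial's main conclusions.

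**What to change.** Collect the NPC Scale-SF at t0, before randomisation, from nurses in both arms, and correlate it with the t0 KCS-Nurse, accounting for clustering. All nurses are then untrained by the Bundle and the sample has not yet been reduced by dropout. The cost is a baseline survey longer by one 35-item form; if the form is moved from t1, the total burden is unchanged.

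If t0 has passed, state that the NPC Scale-SF is paired with the t1 KCS-Nurse and that the correlation is estimated within arm or adjusted for arm, accounting for clustering. This costs no extra data collection. A separate estimate for each arm is less precise: with 48 nurses (half of 96) and r = 0.50, the 95% interval ignoring clustering is 0.252 to 0.687. Adjustment for arm keeps all nurses in one estimate. Neither would repair a change in the spread of scores, or in the within-arm correlation itself, caused by training, so the t0 pairing is preferable where it is still possible.

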### Setting

The trial will be conducted over approximately 6 months in 24 aged care homes across three Australian states: Victoria, Queensland, and South Australia. Residential aged care homes provide accommodation and 24-h personal care for older people (aged 65 + years) who can no longer live in their own home [19, 20]. Most aged care in Australia is subsidized and regulated by the Commonwealth government and includes nursing and other general healthcare, but not acute or sub-acute medical care, which falls under state and territory jurisdictions.

The number of sites allows for a diverse sample that reflects the profile of the residential aged care sector in each state. During recruitment, homes will be stratified according to three sizes (small, 60 or fewer residents; medium, 61–100 residents; large, 101 + residents) to ensure a representative sample. We will aim to recruit a diverse sample regarding other site characteristics (e.g. ownership structure, location). In a larger future trial, formally stratifying for these characteristics will be considered.

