### Secondary outcomes

The secondary outcomes include data likely to be used in a larger definitive trial to test the effectiveness of the intervention. The compatibility of the *Bundle* with current residential aged care catheter care practices, procedures and policies will be assessed through a pre- and post-intervention audit of each residential aged care home IDC-related organisational policies and practices, as well as post-intervention semi-structured interviews with managers/senior leaders about their organisational IDC policies and practices.

Pilot data on the preliminary effects of the *Bundle* on rates of IDC-related complications will be assessed through a pre- and post-retrospective review of medical records of residents with an IDC. Records will be reviewed for incidences of CAUTI (symptomatic and asymptomatic), catheter blockages, catheter-related trauma, leakage/bypassing, and hospitalisations related to catheter complications. Pilot data on the effects of the *Bundle* on nurses’ knowledge and confidence providing IDC care will be assessed through the *Nurses’ Catheter Care Knowledge and Confidence Scale* (KCS-Nurse), a study-specific survey of nurses’ knowledge and confidence.

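### On the best-supported reading of t1, the second clinical record review covers none of the 3-month application phase, so the pilot complication data would largely describe care before training was complete

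*Protocol article*

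**What the plan says.** The Intervention section delivers the Bundle in "two consecutive phases, (1) education phase and (2) application to practice phase". The next section but one in that sequence fixes when the second phase starts and how long it lasts: "Phase 2 runs for 3 months after participating staff from each site have completed the course and workshop". The Setting section gives the overall length: "The trial will be conducted over approximately 6 months in 24 aged care homes".

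Resident complications come from one instrument, the "IDC-IMPROVE Clinical Data Extraction Form". Table 1 lists it at t0 and t1 in both arms, with no t2 entry. It records catheter changes and complications and "number of admissions to hospital and emergency departments for IDC-related complications for residents with an IDC for the prior 3 months". Secondary outcomes states the use: preliminary effects of the Bundle on complication rates "will be assessed through a pre- and post-retrospective review of medical records of residents with an IDC".

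Other entries bear on what t1 and t2 mean:

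- Table 1 puts the nurses' course feedback survey at t1. The workshop feedback survey is also at t1, described as "An online survey nurses will be asked to complete at the end of the catheterisation skills workshop".
- Table 1 puts the organisational audit, described as before and after the intervention, at t0 and t2, and the interviews at t2.
- The completion and withdrawal record, which follows staff through both phases, is at t0, t1 and t2.
- Data analysis speaks of "reporting at baseline (t_0_), post-intervention (t_1_), and follow-up (t_2_) timepoints".

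Table 2, which holds the timeline, is not shown in the text available.

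**The concern.** A retrospective review describes only the months before the day it is done. If that day is the end of training, its 3 months end where supported practice begins. Trained nurses and care workers apply the Bundle, with coaching, in the following 3 months, and no later extraction of resident records is listed.

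The stake is the pilot information on how complications change under the Bundle. Secondary outcomes says these data are likely to be used in a definitive trial. A before-after or between-arm contrast from the second review would largely reflect care while training was incomplete, and might be taken as a first look at the effect of the Bundle. The same form is the only listed instrument that records the number of catheter changes and which staff perform them, so the record of that practice change would be missed in Phase 2 as well.

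**Working it through.** The plan gives no figure for the coverage of the review window, so there is none to reproduce. The check has two steps.

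**Step 1: where t1 falls.** The entries side by side:

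| Entry | t1 = end of education | t1 = end of Phase 2 |
|---|---|---|
| Workshop survey at t1, completed as the workshop ends | fits | conflicts (about 3 months late) |
| Course survey at t1 | fits | awkward |
| Completion record over both phases at t0, t1, t2 | fits enrolment, end of education, end of application | possible |
| Before-and-after audit at t0 and t2; interviews at t2 | fits | also fits |
| Data analysis label of t1 as post-intervention | fits only if it means after education | fits |

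The workshop survey separates the two readings most sharply, and it points to the end of education.

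**Step 2: what the window covers.** Inputs:

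- Look-back: 3 months (Table 1).
- Phase 2: 3 months, starting after the course and workshop (Phase 2 section).
- Trial length: about 6 months (Setting).
- E, the months from the baseline extraction to the end of education, is not stated. Assumption: 1 to 3 months, because 6 − 3 = 3 leaves at most about 3.

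Put the baseline extraction at month 0. The baseline window is then −3 to 0, and Phase 2 runs from E to E + 3.

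If t1 is the end of education, the second window runs from E − 3 to E:

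- Phase 2 covered: the window ends at E, where Phase 2 begins, so E − E = 0 months for any E.
- Overlap with the baseline window: 3 − E months when E is below 3, otherwise 0.
- The remainder, E months up to a maximum of 3, lies between baseline and the end of education.

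| E (months) | Repeats baseline window | Baseline to end of education | Phase 2 |
|---|---|---|---|
| 1 | 2.0 | 1.0 | 0 of 3 |
| 1.5 | 1.5 | 1.5 | 0 of 3 |
| 2 | 1.0 | 2.0 | 0 of 3 |
| 2.5 | 0.5 | 2.5 | 0 of 3 |
| 3 | 0 | 3.0 | 0 of 3 |

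If the second extraction is done at the end of Phase 2, the window runs from E to E + 3. It covers 3.0 of 3.0 months of Phase 2 and no earlier time, for every E in the table.

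**The case against.** The strongest reply is that the text never dates t1. Table 2 does, and it is not shown. The one explicit label, in Data analysis, calls t1 post-intervention and t2 follow-up, and the intervention comprises both phases. Read that way, t1 is the end of Phase 2, the 3-month look-back matches the 3-month phase exactly, and the before-and-after review at t0 and t1 makes sense. The audit and interviews at t2 do not rule this out, since a later follow-up is also after the intervention.

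This stands as a reason for caution. It does not remove the point, because a survey completed as the workshop ends cannot sit at a timepoint about 3 months later. One of the two passages needs correcting on either reading.

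Three limits on the harm also stand:

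- Overlap with the baseline window depends on E, which the plan does not give; at E = 3 there is none.
- The outcome is secondary and descriptive. In Table 3 the extraction form counts only towards the 75% data-completeness threshold, so no progression criterion depends on complication rates.
- The nurses' course is self-paced, so practice may begin to change during education. A reader might infer that a real benefit would show as no difference at all. That assumes no change until training ends, which the plan does not say.

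**Conclusion.** The point holds in a conditional form. On the best-supported reading, with t1 at the end of education, the second record review covers 0 of 3 months of Phase 2 for any length of education. With education assumed to end 1 to 3 months after baseline, it also repeats between 2 and 0 months of the baseline window. For residents present in both reviews, events in the repeated months would count both as before and as after. The pilot data on the Bundle's preliminary effect on complications would then largely describe care before training was complete.

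Two stronger conclusions might be drawn, and the protocol does not support them. One is that Phase 2 goes unmeasured altogether: the nurse and care-worker knowledge and confidence scales, the audit and the interviews are all taken at t2, so the gap is confined to the resident record data. The other is that the objective of gathering pilot data on complications fails outright: the objective is descriptive, and the baseline extraction in all 24 homes and the control-arm data still give usual-care rates.

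The conclusion rests on inferring t1 from Table 1 and the phase description. If Table 2 puts t1 at the end of Phase 2, coverage is complete and the remaining fault is the inconsistent labelling. This should be fixed, but it does not threaten the primary feasibility outcome.

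**What to change.** Define t1 and t2 relative to the two phases, and reconcile Table 1 with the labels in Data analysis. Then tie the second clinical extraction to the end of Phase 2, with matched dates in control homes, so that the existing 3-month look-back coincides with Phase 2. If t1 is the end of education, this means listing the form at t2 in place of t1.

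Tying the extraction to the phase is safer than simply changing t1 to t2. If t1 turned out to be the end of Phase 2, moving to a later t2 would shift the window away from the phase it should cover.

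The amendment is small. The number of extractions is unchanged, and managers already complete the audit at t2. The downside is that clinical data arrive about 3 months later.
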